GnRH antagonists have a reported failure rate of approximately 0.34–8.0% for controlling premature LH surges in women with a normal ovarian reserve [1–3]. An antagonist failure is more likely to occur in women with advanced age, a diminished ovarian reserve and poor response to gonadotropins [15]. Our prospective trial in a population of poor responders showed that ovulation of the dominant follicle was controlled well using progestin administered orally as a surrogate for a GnRH antagonist, with low incidence rates of LH surges and premature ovulation (3.0%) [8]. Moreover, progestin priming prolonged the follicular phase by one more day, and the diameter of the pre-ovulatory follicle was larger than those of natural cycle patients. These data indicated that progestin treatment significantly suppressed follicular rupture and provided a wide window for oocyte retrieval [8]. Therefore, we assumed that progestin may show some superiority in controlling premature LH surges compared with GnRH antagonists in poor responders. Thus, we have developed this well-designed large-sample prospective trial to investigate the potential of progestin for poor responders undergoing IVF treatment.

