### Statistics

#### Sample size and power calculations

For the power calculation, previous studies reported that the incidence of premature LH surges in the GnRH antagonist protocol was 8.0%, and our recent data show that the incidence of premature LH surges and ovulation was 3.0% in poor responders using the PPOS protocol. Therefore, we hypothesise that the administration of MPA would decrease the incidence of premature LH surges. The superiority margin is 4.0%. A sample size of 166 in each group would yield 90% power to establish superiority at the 0.01 level of significance, and 109 in each group yield 90% power to establish superiority at 0.05 level of significance [16]. Given the abundant clinical resources in our clinic, the number of participants is set as 170 in each group in this trial.

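### The 90% power for superiority is not there: 166 and 109 per group match a non-inferiority calculation, and 170 per group gives about 53% power for the planned chi-square test at two-sided 0.05

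*Protocol article*

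**What the plan says.** All the inputs are in the protocol article, under Sample size and power calculations:

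- Antagonist rate: "the incidence of premature LH surges in the GnRH antagonist protocol was 8.0" percent.
- PPOS rate: "the incidence of premature LH surges and ovulation was 3.0% in poor responders using the PPOS protocol".
- Direction: "we hypothesise that the administration of MPA would decrease the incidence of premature LH surges".
- Margin: "The superiority margin is 4.0" percent.
- Size for the stricter level: "A sample size of 166 in each group would yield 90% power to establish superiority at the 0.01 level of significance".
- Size for the conventional level: "109 in each group yield 90% power to establish superiority at 0.05 level of significance".
- Decision: "the number of participants is set as 170 in each group in this trial".

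The text does not say whether these significance levels are one-sided or two-sided, and it shows no formula; it cites a reference. The Statistical analysis section plans an intention-to-treat chi-square comparison of the primary outcome, with significance at p < 0.05. That test carries no margin. The article contains no non-inferiority hypothesis.

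**The concern.** A fall from 8% to 3% is a 5-point difference between two small proportions, and 109 per group is far too few to detect it with 90% power. Using the margin should make matters worse. To show superiority by more than 4 points, the margin is subtracted from the expected difference, which leaves 1 point and calls for thousands per group. Sizes in the low hundreds suggest that the margin entered with the opposite sign.

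At stake is the power claim for the primary outcome. The article treats 170 per group as more than enough, when for the stated aim it is far short. A reader who trusts 90% power would take a non-significant result as good evidence that the regimens control surges equally well. A 4-point margin with no role in the planned test also leaves room to recast the question as non-inferiority after the data are seen.

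**Working it through.** **Inputs.** p_A = 0.08 and p_P = 0.03; margin 0.04; power 90%; 1:1 allocation (Randomisation section); 170 per group; chi-square test at 0.05 (Statistical analysis section).

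**Formula.** Unpooled normal approximation, n per group:

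n = [p_A(1 − p_A) + p_P(1 − p_P)] × (z_α + z_0.90)² / D²

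The variance sum is 0.08 × 0.92 + 0.03 × 0.97 = 0.0736 + 0.0291 = 0.1027. For one-sided alpha, (z_α + z_0.90)² is 8.564 at 0.05 and 13.017 at 0.01.

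**Step 1: reproduce the stated sizes.** Take D = 0.05 + 0.04 = 0.09, so D² = 0.0081.

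- 0.05: 0.1027 × 8.564 / 0.0081 = 108.58, rounded up to **109**.
- 0.01: 0.1027 × 13.017 / 0.0081 = 165.04, rounded up to **166**.

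Both match. With the difference written as antagonist minus PPOS, this is the size for rejecting p_A − p_P ≤ −0.04, that is, for excluding a PPOS rate more than 4 points higher.

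**Step 2: sizes for superiority at 90% power.**

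| Aim | D | One-sided 0.05 | One-sided 0.01 |
|---|---|---|---|
| PPOS lower by any amount | 0.05 | 352 | 535 |
| PPOS lower by more than 4 points | 0.05 − 0.04 = 0.01 | 8,796 | 13,369 |

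For the any-difference test at two-sided 0.05, the unpooled formula gives 0.1027 × 10.507 / 0.0025 = 431.6, or 432; the pooled-variance version gives 435. At two-sided 0.01 the figures are 612 and 617. Reading 4 points as the difference to detect gives at least 507. None of these is near 109 or 166.

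**Step 3: power of the planned test at 8% versus 3%.** By normal approximation with 170 per group, SE = √(0.1027/170) = 0.02458 and 0.05/0.02458 = 2.034. Power at two-sided 0.05 is Φ(2.034 − 1.960) = 53%. Exact binomial enumeration of the chi-square test gives:

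| n per group | Two-sided alpha | Uncorrected | Continuity-corrected |
|---|---|---|---|
| 170 | 0.05 | 53.1% | 43.8% |
| 170 | 0.01 | 27.7% | 19.8% |
| 166 | 0.01 | 26.7% | 18.9% |
| 109 | 0.05 | 36.2% | 24.5% |

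The most favourable reading, a one-sided 0.05 test with 170 per group, gives 65% by normal approximation and 67% exactly.

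**Step 4: power for superiority by more than 4 points, 170 per group.** 0.01/0.02458 = 0.407. Power is Φ(0.407 − 1.645) = 11% at one-sided 0.05 and Φ(0.407 − 1.960) = 6% at one-sided 0.025.

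**Step 5: sensitivity to the antagonist rate** (PPOS 3%, 170 per group, two-sided 0.05, exact):

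| Antagonist rate | Uncorrected | Continuity-corrected |
|---|---|---|
| 4% | 7% | 4% |
| 6% | 26% | 18% |
| 8% | 53% | 44% |
| 10.5% | 81% | 75% |
| 12% | 91% | 87% |

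**The case against.** - **The formula is not shown, so the sign error is inferred.** True. The cited reference was not available for this check. Two exact matches at two significance levels make the inference strong, but the shortfall does not depend on it: the stated rates, the group size and the planned test are enough to show that power is not 90%.
- **The details may be in the analysis plan.** This is not an omission. The article prints a power figure that its own inputs contradict, and no later document can make it true.
- **8.0% may be conservative here.** The Background says: "GnRH antagonists have a reported failure rate of approximately 0.34–8.0% for controlling premature LH surges in women with a normal ovarian reserve". So 8.0% is the top of a range from a different population. But the Background goes on to say that antagonist failure is more likely with advanced age, diminished reserve and poor response, and the Discussion agrees. A true rate above 8% is therefore plausible on the protocol's own reasoning. This stands as a caution: the choice of 8.0% cannot be called optimistic from this document alone. It does not rescue the claim, because power is stated at 8.0%, and 90% needs a rate near 12%.
- **The error leaves the analysis intact.** Also true. Type I error, the estimate and the planned test are unaffected, and nothing in the article says that a null result would be read as equivalence. The defect is the false power claim for the primary outcome, which governs how much weight a null result can bear.

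**Conclusion.** The concern holds. For the stated aim and the planned test, 170 per group gives about 53% power at two-sided 0.05 (44% with continuity correction), not 90%. At 0.01 it gives about 28%. No choice of sidedness reaches 90%; the best is about 67%. If the 4-point margin is taken literally as a superiority margin, power is 6% to 11%. Reaching 90% with the planned test would take about 435 per group, roughly 2.6 times the plan (435/170).

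These figures rest on the article's own rates of 8.0% and 3.0%, 170 evaluable participants per group, and no loss to follow-up. That the margin was added rather than subtracted is inferred from the exact reproduction of 166 and 109. The size of the shortfall does not rest on that inference.

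**What to change.** Correct the sample-size paragraph, by amendment or in the analysis plan, before the data are analysed:

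1. Withdraw the statement that 166 and 109 per group give 90% power for superiority. If the figures are kept for the record, say that they correspond to one-sided 0.01 and 0.05 sizes for excluding a PPOS rate more than 4 points higher, and that the trial tests no such hypothesis.
2. Withdraw the 4-point margin, since the planned test does not use it.
3. State that 170 per group gives about 53% power at 8% versus 3% for the two-sided 0.05 chi-square test, and specify whether a continuity correction applies (44% if it does).
4. Add a short table of power against the antagonist rate, as in Step 5, showing that about 80% and 90% are reached only near 10.5% and 12% with the uncorrected test. Keep to rates above the assumed 3% for PPOS. Below that, as at 0.34%, any rejection would almost always favour the antagonist and is not power for this hypothesis.
5. State that a non-significant result will not be read as equivalence or non-inferiority, and that the difference will be reported with its confidence interval.

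The cost is a wording change and a less favourable power statement. It needs no extra participants and no change to treatment or to the planned test.

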### Data management

The timepoints of enrolment, intervention, data collection and follow-up are described in Fig. 2. Data collected are entered into our electronic data capture system and stored on a secure server at Shanghai Ninth People’s Hospital. An automated system for validating data against a set of predefined rules will query investigators regarding data that are invalid, illogical or incomplete. Data elements critical to the primary aim of this trial are double-checked to confirm the accuracy of the data entered compared with the source documents.

**Fig. 2 Fig2:**
[figure not shown]
SPIRIT diagram for this protocol comparing PPOS with GnRH antagonist in poor responders. GnRH gonadotrophin-releasing hormone, PPOS progestin-primed ovarian stimulation

### Statistical analysis

We will utilise an intention-to-treat approach with a chi-square test to examine differences in the incidence of premature LH surges. Secondary efficacy parameters and safety parameters will be analysed using a chi-square test for enumeration data and Student’s *t* test for measurement data. *p* < 0.05 is considered as a significant difference.

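### The stated 4-point superiority margin and 90% power do not belong to the planned primary test, a chi-square test of zero difference at p<0.05

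*Protocol article*

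**What the plan says.** In the protocol article, Sample size and power calculations takes two planning rates: "the incidence of premature LH surges in the GnRH antagonist protocol was 8.0" percent, and "the incidence of premature LH surges and ovulation was 3.0% in poor responders using the PPOS protocol". From these it hypothesises that MPA lowers the incidence of surges. It then adds "The superiority margin is 4.0" percent and gives two sizes. The first reads: "A sample size of 166 in each group would yield 90% power to establish superiority at the 0.01 level of significance". The second, for the same power at the 0.05 level, is 109 per group. The number is set at 170 per group because clinical resources are ample. Neither level is named as the one that governs, and sidedness is not given.

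Statistical analysis fixes the primary test: "We will utilise an intention-to-treat approach with a chi-square test to examine differences in the incidence of premature LH surges". The threshold is p below the level at which "0.05 is considered as a significant difference". This section mentions no margin and no shifted null hypothesis.

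**The concern.** An ordinary chi-square test for two proportions asks whether the difference is zero. Rejecting that null does not show that the difference exceeds 4 points, so the test cannot deliver superiority by the stated margin. Either the margin is part of the claim and the test is wrong for it, or the test is right and the margin should not be there.

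The power statement depends on the answer. A reader will take 90% as the chance that the planned primary analysis succeeds if the planning rates are true. If 90% was calculated for another hypothesis, the trial's real chance of success is unknown to the reader, and a non-significant result could be read as stronger evidence against a benefit than it is.

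**Working it through.** **Inputs** (Sample size and power calculations, unless noted): antagonist rate 0.08; PPOS rate 0.03; expected difference 0.05; margin 0.04; power 90% (z = 1.2816); 170 per group; 1:1 allocation (Randomisation).

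Unpooled variance term: V = 0.08×0.92 + 0.03×0.97 = 0.0736 + 0.0291 = 0.1027.

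**1. Reproducing 166 and 109.** Use n = (z_α + z_β)² × V / D², with D = 0.05 + 0.04 = 0.09 (margin added) and one-sided α.

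- α = 0.01: (2.3263 + 1.2816)² = 13.017; 13.017 × 0.1027 / 0.0081 = 165.04, rounded up to 166.
- α = 0.05: (1.6449 + 1.2816)² = 8.564; 8.564 × 0.1027 / 0.0081 = 108.58, rounded up to 109.

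Both published figures match. Adding the margin to the effect tests the null that PPOS is worse by at least 4 points, which is non-inferiority.

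**2. Other hypotheses, 90% power, per group.**

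| Hypothesis | α = 0.01, one-/two-sided | α = 0.05, one-/two-sided |
|---|---|---|
| Zero difference (pooled variance under the null) | 539 / 617 | 355 / 435 |
| Better by more than 4 points (D = 0.05 − 0.04 = 0.01) | 13,369 / 15,282 | 8,796 / 10,792 |
| Not worse by 4 points (D = 0.09) | **166** / 189 | **109** / 134 |

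Only the one-sided entries in the last row match the protocol.

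**3. Power at 170 per group, 8% versus 3%.** Standard error of the difference: √(0.1027/170) = 0.02458. Under the zero null, with mean rate 0.055: √(2×0.055×0.945/170) = 0.02473.

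- Chi-square, two-sided 0.05: Φ((0.05 − 1.96×0.02473)/0.02458) = 52%. Exact enumeration of the uncorrected test gives 53%; with continuity correction, 44%.
- Chi-square, two-sided 0.01: 29% by the normal approximation, 28% exact.
- Lower limit of a two-sided 95% interval above 4 points: Φ(0.01/0.02458 − 1.96) = 6%; exact enumeration with the Wald interval gives 5%.
- Not worse by 4 points, one-sided 0.01: Φ(0.09/0.02458 − 2.326) = 91%. This is where the stated 90% belongs.

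**4. What results near the planning rates would show.** Wald 95% intervals, antagonist minus PPOS, 170 per group.

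| Surges, antagonist vs PPOS | Difference (points) | Uncorrected p | 95% interval (points) | Significant at 0.05? | More than 4 points shown? |
|---|---|---|---|---|---|
| 14 vs 5 (8.2% vs 2.9%) | 5.3 | 0.034 | 0.4 to 10.1 | yes | no |
| 17 vs 5 (10.0% vs 2.9%) | 7.1 | 0.008 | 1.9 to 12.2 | yes | no |
| 22 vs 5 (12.9% vs 2.9%) | 10.0 | <0.001 | 4.4 to 15.6 | yes | yes |

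With 5 surges on PPOS, 22 on the antagonist is the smallest count whose Wald interval clears 4 points.

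**The case against.** The strongest reply is that the article states only one decision rule, the chi-square at p<0.05. The margin appears only as a sizing input. The hypothesis beside it is directional with no threshold, and the Background speaks only of some superiority. A zero-difference test fits that aim. This stands: the test is not the faulty element, and the margin and the power statement are what must change.

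A reader might also infer a conflict of significance levels, because 170 lies just above 166 and that figure goes with "90% power to establish superiority at the 0.01 level of significance". The document does not establish this. The same sentence gives a 0.05 size of 109, which agrees with the analysis section, and nothing says that the trial will be judged at 0.01. Choosing a number that also covers a stricter level and then testing at 0.05 is not a contradiction. It follows that the text does not support saying that three competing decision rules coexist. What remains is that the governing level and its sidedness are not named where the size is set.

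Nor should the absence of a risk difference and confidence interval be counted against the plan. A condensed article may leave these to the full protocol or the SAP.

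Finally, the 14 versus 5 example depends on the version of the test: with continuity correction p is 0.059, and the article does not say which version applies. Power with the correction is lower still (44%), so the conclusion about power does not depend on this choice.

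**Conclusion.** The point holds as a mismatch between the sample-size section and the primary test. The 4.0-point margin is called a superiority margin, entered the calculation as a non-inferiority margin, and is absent from the analysis. The stated 90% belongs neither to the planned chi-square (about 53% at two-sided 0.05, about 28% at 0.01) nor to superiority by more than 4 points (about 5% with a two-sided 95% interval).

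These figures assume 8% and 3% as the true rates, 170 analysed per group and, for the 53% and 28%, an uncorrected chi-square. That the margin was added to the effect is inferred from the exact match to both published sizes; the article does not show its formula.

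**What to change.** State one null hypothesis and one significance level, with its sidedness, in both Sample size and power calculations and Statistical analysis. Since the stated aim is that MPA decreases surges:

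- keep superiority against zero difference, by chi-square at two-sided 0.05;
- delete the 4.0% superiority margin;
- say that the 0.01 figure is not the decision level;
- withdraw the 90% statement with its sizes of 166 and 109, and report about 53% power at 170 per group for 8% versus 3%.

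Relabelling 4 points as a non-inferiority margin would match the arithmetic, but it would introduce a hypothesis that the protocol never states. Putting a true 4-point superiority margin into the test would leave almost no power at this size.

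The cost is wording before analysis, with no new data. The downside is a much less favourable stated power. Rewording does not restore it: 90% for the planned test at two-sided 0.05 would need 435 per group.

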### In vitro fertilisation and embryo culture

All follicles more than 10 mm will be retrieved. Follicles are flushed three times at most if no cumulus oocyte complex is present. Standard insemination or ICSI is performed within 6 h of retrieval. Embryos are examined for the number and regularity of blastomeres and the degree of embryonic fragmentation on the third day. If available, two top-quality embryos (including grade I and grade II, eight-cell blastomere embryos) in the GnRH antagonist group are transferred on the third day. The remaining top-quality embryos are frozen by vitrification, while the non-top-quality embryos are cultured for an extended time. Only blastocysts with good morphology are frozen on day 5 or 6. All top-quality cleavage embryos and the cryopreserved blastocysts are recorded as viable embryos. In the PPOS group, all top-quality embryos are frozen on the third day, while the non-top-quality embryos are cultured for an extended time and cryopreserved according to the same criteria as above.

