### Endometrium preparation and frozen-thawed embryo transfer

Endometrium preparation uses either mild stimulation or hormone replacement therapy. For mild stimulation frozen-thawed embryo transfer cycles, we prescribe letrozole 2.5–5 mg for 3–5 days from cycle day 3 and then monitor follicular growth via serum hormone levels and ultrasound from cycle day 10. At times, treatment includes a low dose of hMG (75 IU/day) to stimulate follicle growth and the endometrial lining. When the diameter of the dominant follicle is >16 mm and the endometrial thickness is > 8 mm, with *E*_2_ > 150 pg/ml and progesterone <1.0 ng/ml, one of two procedures is performed, depending upon the LH level. If the serum LH level is <20 mIU/ml, 5000 IU of hCG is administered at night (21:00) to trigger ovulation, and the transfer of cleavage embryos is arranged for 5 days later. If the LH level is >20 mIU/ml, 5000 IU of hCG is injected the same afternoon, and the transfer is conducted 4 days later. The blastocyst transfer is arranged on the sixth or seventh day depending on serum hormone levels and ultrasound results. Dydrogesterone (Abbott Biologicals BV, the Netherlands) was administered orally at 40 mg/day and micronised progesterone capsules at 400 mg/day was administered vaginally for luteal support beginning on the third day after hCG injection.

For patients with a thin endometrium or where the frozen-thawed embryo transfer fails after stimulation cycles, hormone replacement therapy is recommended for endometrial preparation, specifically ethinyl oestradiol administered orally at 75 mcg/day from cycle day 3 onwards, which is commonly used for 14 days. Once the endometrial lining is >8 mm thick, Femoston (a yellow tablet) is administered twice per day (Abbott Healthcare Products BV, Weesp, the Netherlands), and 400 mg micronised progesterone capsules are administered daily via an intravaginal route. The time for thawing and transfer is determined on the third day after progesterone administration. The maximum number of transferred embryos is two per cycle. When pregnancy is achieved, the progesterone supplement is continued until 10 weeks of gestation.

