#### Secondary outcomes

Secondary efficacy parameters include the number of oocytes retrieved, the number of viable embryos, the clinical pregnancy rate, the implantation rate, the ongoing pregnancy rate and the cumulative live birth rates from a single IVF cycle. Clinical pregnancy will be defined as the presence of an intrauterine gestation sac at 7 weeks of gestation. Ongoing pregnancy will be defined as a viable pregnancy at 12 weeks of gestation.

The safety endpoints include the incidence rates of ovarian hyperstimulation syndrome, miscarriage, ectopic pregnancy, pregnancy complication, congenital anomalies and neonatal complications.

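### The implantation rate is assigned a chi-square test, which, on the usual per-embryo count, ignores correlation between embryos of the same woman and gives p-values that are too small

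*Protocol article*

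**What the plan says.** The Statistical analysis section gives a single rule for secondary outcomes: "Secondary efficacy parameters and safety parameters will be analysed using a chi-square test for enumeration data", with a t test for measurement data and significance at p below 0.05. It mentions no allowance for several observations from one woman.

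Secondary outcomes lists "the clinical pregnancy rate, the implantation rate, the ongoing pregnancy rate and the cumulative live birth rates from a single IVF cycle". Clinical pregnancy is a presence-or-absence result: "Clinical pregnancy will be defined as the presence of an intrauterine gestation sac at 7 weeks of gestation". The implantation rate gets no definition of its own.

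The Randomisation section allocates participants, that is women, 1:1. In vitro fertilisation and embryo culture says that "two top-quality embryos (including grade I and grade II, eight-cell blastomere embryos) in the GnRH antagonist group are transferred" on day 3, on condition that two are available. It adds, for the same arm, "The remaining top-quality embryos are frozen by vitrification". For frozen transfers, "The maximum number of transferred embryos is two per cycle", and the same section provides for a different endometrial preparation after a failed frozen transfer. So a woman can contribute more than one embryo to a transfer, and more than one transfer.

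**The concern.** The Pearson chi-square test assumes that the units counted are independent. Two embryos placed together share the woman, the oocyte cohort, the endometrium and the cycle. Embryos from successive transfers still share the woman and the cohort. If their outcomes are positively correlated, the embryo count overstates the information in the data. The standard error is then too small, and a difference between arms is declared significant too often.

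What is at stake is the p-value and interval for one secondary outcome. A nominally significant implantation result could be read as support for one stimulation regimen when the evidence is weaker than it looks.

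**Working it through.** The plan states no rate, power or sample size for implantation, so there is no figure of its own to reproduce.

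**Inputs from the protocol article.** Nominal level 0.05 (Statistical analysis; sidedness is not stated and is taken as two-sided, as a chi-square test is). One or two embryos per transfer, and repeat transfers possible (In vitro fertilisation and embryo culture; Endometrium preparation and frozen-thawed embryo transfer). Unit of randomisation: the woman (Randomisation).

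**Assumptions, because the article gives no figure.** Implantation is counted per embryo. The intra-woman correlation (ICC) is 0.1 to 0.5. The number of embryos per woman, m, is as shown below.

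**Formulas.** Design effect DE = 1 + (Σm²/Σm − 1) × ICC. Actual two-sided error = 2 × [1 − Φ(1.96/√DE)].

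- All women contribute two: Σm²/Σm = 4/2 = 2, so DE = 1 + ICC.
- Half contribute two and half one: Σm²/Σm = (4 + 1)/(2 + 1) = 1.667, so DE = 1 + 0.667 × ICC.
- Mix of 1, 2, 3 and 4 embryos over repeat transfers in 40/40/10/10% of women: Σm²/Σm = 4.5/1.9 = 2.368, so DE = 1 + 1.368 × ICC.

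| ICC | Half two, half one: DE, actual error | All two: DE, actual error | Mix of 1 to 4: DE, actual error |
|---|---|---|---|
| 0 | 1.000, 5.0% | 1.0, 5.0% | 1.000, 5.0% |
| 0.1 | 1.067, 5.8% | 1.1, 6.2% | 1.137, 6.6% |
| 0.2 | 1.133, 6.6% | 1.2, 7.4% | 1.274, 8.2% |
| 0.3 | 1.200, 7.4% | 1.3, 8.6% | 1.411, 9.9% |
| 0.5 | 1.333, 9.0% | 1.5, 11.0% | 1.684, 13.1% |

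**Check by simulation** (beta-binomial; 20,000 runs; 100 women with a transfer per arm; 60% of transfers with two embryos; implantation 20%; where repeats are simulated, 40% of women with a failed transfer have another; all of these are assumptions). At ICC 0.1, 0.2, 0.3 and 0.5 the actual error of the embryo-level test is:

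- one transfer per woman in both arms: 6.0%, 7.1%, 7.7%, 9.7%;
- repeats after failure counted in both arms: 6.4%, 7.2%, 8.4%, 10.6%;
- repeats counted in one arm only: 6.1%, 8.4%, 10.0%, 15.5%.

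At ICC 0 all three give 5.0-5.1%.

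The last scenario is an extreme, and the article does not say that counting will differ by arm. It also shows a separate effect. At ICC 0.2 the embryo-level rates are 20.0% and 18.8% with no treatment effect, because women whose transfers fail add more embryos to the denominator. Clustering corrects the standard error but does not remove that shift.

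**The case against.** The strongest reply is that the per-embryo unit is not written down. If the rate were computed as one proportion per woman and compared by t test as measurement data, clustering within women would not arise. That is correct, and the point is conditional on the per-embryo reading. That reading is still the natural one: implantation is listed alongside clinical pregnancy, which is already defined by presence of a sac, and a separate rate adds information mainly when counted per embryo.

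It could also be said that such detail belongs in a fuller document. A missing definition may, but the test itself is stated here, for all secondary enumeration data.

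The size is easily overstated. Two embryos are transferred only if available, and these are poor responders, so single-embryo transfers are plausible. With only 30% of women contributing two, the error at ICC 0.2 is 6.1%. A reader might extrapolate to three embryos for every woman and obtain 10-17% at ICC 0.2 to 0.5; nothing in the article supports that pattern.

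A reader might also infer that the pregnancy and live-birth comparisons are not by intention to treat. The documents do not support this. The Abstract says the data analysis is by intention to treat, cumulative live birth is given per single IVF cycle, and nowhere is a per-transfer denominator stated for these outcomes. The limitation applies to the implantation rate alone, because a woman with no transfer contributes no embryo to it.

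**Conclusion.** The concern holds for the implantation rate on its ordinary per-embryo meaning. The planned chi-square test would then be anticonservative: about 6-9% actual error at a nominal 5% if half the women contribute two embryos and the rest one, and about 6-11% if all contribute two. Repeat transfers could raise this further. These figures rest on an assumed positive ICC of 0.1 to 0.5; with no correlation the test keeps its 5% level. Two embryos in a single transfer are enough for the problem, so it does not depend on whether repeat transfers are counted.

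The inflation is modest and confined to one secondary outcome. The primary outcome, LH on the trigger day, is one result per woman and is unaffected, as is the sample size.

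**What to change.** Except the implantation rate from the general chi-square rule and do one of the following:

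- analyse it with a method clustered on the woman: a GEE logistic model with robust variance, or a bootstrap of the ratio that resamples women; or
- report the per-embryo rate by arm descriptively, without a p-value.

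In either case, label it as not an intention-to-treat comparison, since women without a transfer are left out. When making the change, write out the denominator and say whether first or all transfers count, with the same rule in both arms.

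The cost is a sentence or two of analysis wording and minor programming. The interval widens by a factor of √DE: √1.067 = 1.03 at the low end (half of women with two embryos, ICC 0.1) and √1.5 = 1.22 at the high end (all with two, ICC 0.5). Design, sample size and the primary analysis stay as they are.

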### Participants

#### Inclusion criteria

The following are the inclusion criteria:Women who have a history of infertility ≥1 yearWomen aged >22 and <42 yearsWomen with spontaneous menstrual cycles of 21–35 daysWomen who have at least one of the following indications for IVF or ICSI: tubal factor, male factor, diminished ovarian reserve, endometriosis or unexplained factorsWomen diagnosed as poor responders according to the Bologna criteria, including at least two of the three following criteria:Advanced age (≥40 years) or any other risk factor for poor ovarian responseA previous poor response with no more than three oocytes retrieved using the conventional stimulation protocolsAbnormal ovarian reserve test results, including bilateral antral follicle counts <7 or serum anti-Müllerian hormone <1.1 ng/ml

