### Randomisation

Participants will be allocated randomly into one of the two arms at a ratio of 1:1 on menstrual cycle day 3. The allocation sequence will be generated utilising computer-generated random numbers. Both investigators and participants will be aware of the allocation after ovarian stimulation. The doctors and embryologists involved in oocyte retrieval and embryo transfer are blinded to the group assignments of the participants in the trial.

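### Oocyte and viable-embryo counts are assigned to an unadjusted t test although age is known for every woman: a modest, avoidable loss of precision on two secondary outcomes

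*Protocol article*

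**What the plan says.** The Secondary outcomes section of the protocol article begins: "Secondary efficacy parameters include the number of oocytes retrieved, the number of viable embryos". The Statistical analysis section then sends secondary efficacy and safety parameters to one of two tests: chi-square for enumeration data and Student's t "test for measurement data". The two counts fall under the t test, and no covariate is named. The primary outcome is handled separately, by a "chi-square test to examine differences in the incidence of premature LH surges".

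The Inclusion criteria section sets an age range (over 22 and under 42), so age is known for everyone. Women must also be poor responders, "including at least two of the three following criteria": advanced age or another risk factor, an earlier cycle with a low oocyte yield, and an abnormal reserve test (antral follicle count or anti-Müllerian hormone). Under Randomisation, women are "allocated randomly into one of the two arms at a ratio of 1:1 on menstrual cycle day 3", and no stratification is mentioned.

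**The concern.** The protocol's own eligibility rules treat age and ovarian reserve as markers of poor ovarian response, which is close to what the oocyte count measures. A comparison that ignores such information leaves the variation it explains in the error term. A regression that includes it estimates the same difference in means with a smaller standard error, to the extent that the covariates are related to the outcome.

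At stake is the width of the confidence intervals for the first two secondary efficacy outcomes. Because the article states the test, the point concerns a stated choice and not a missing detail.

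**Working it through.** **Inputs from the article**
- Women per arm: n = 170 (Sample size and power calculations: "the number of participants is set as 170 in each group in this trial").
- Test level: p "< 0.05 is considered as a significant difference" (Statistical analysis). The article does not state sidedness; two-sided is assumed here.
- Standard deviation, expected difference, or variance explained by baseline variables (R²) for either count: none given. Results are therefore in units of the outcome's standard deviation σ, with R² assumed at 0.05, 0.10, 0.20 and 0.30.

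The article's sample size figures concern premature LH surges only. There is no stated figure for the counts to reproduce.

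**Step 1: unadjusted comparison.** Standard error = σ√(2/n) = σ√(2/170) = 0.1085σ. With 80% power as a reference point, the detectable difference is (1.960 + 0.842) × 0.1085σ = 0.304σ.

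**Step 2: adjusted comparison.** The residual variance is σ²(1 − R²). The standard error, and so the interval width, is multiplied by √(1 − R²). The equivalent unadjusted arm size is 170/(1 − R²). Power at a difference of 0.304σ is Φ(2.802/√(1 − R²) − 1.960).

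| Assumed R² | Interval width × | Equivalent n per arm | Extra participants | Detectable difference (80% power) | Power at 0.304σ |
|---|---|---|---|---|---|
| 0 | 1.000 | 170 | 0% | 0.304σ | 80% |
| 0.05 | 0.975 | 179 | 5% | 0.296σ | 82% |
| 0.10 | 0.949 | 189 | 11% | 0.288σ | 84% |
| 0.20 | 0.894 | 212 | 25% | 0.272σ | 88% |
| 0.30 | 0.837 | 243 | 43% | 0.254σ | 92% |

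**Step 3: the price if the covariate is useless.** Adding age to a two-arm model takes the residual degrees of freedom from 340 − 2 = 338 to 340 − 3 = 337, which is negligible.

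**Step 4: which covariates exist for everyone.** Age is certain. A reserve measure is not: two criteria out of three suffice, so a woman can enter on age or another risk factor plus an earlier low yield, with no reserve result needed. Where the reserve criterion is used, it may be met by either of two different tests. A common reserve measure for all women is therefore possible but not guaranteed by the text.

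**The case against.** The strongest reply is that nothing is wrong: a two-sample t test with 170 per arm is valid after 1:1 randomisation, only secondary outcomes without a power target are concerned, and a short article may leave adjusted models to an analysis plan that is not shown. The validity point stands and fixes the weight of this remark. The last point stands only in part: the article does not rule out further models, but it does name the test for these outcomes.

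Four stronger readings are tempting, and the document does not support them.

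- *Age and reserve are strong predictors of both counts.* The article gives no correlation or R². Eligibility restricts age, earlier yield and reserve, which tends to lower the R² that can be reached. Viable embryos also depend on fertilisation and embryo grading. That is why the range starts at 5%, where the gain is about 2 power points.
- *Antral follicle count is already held for every woman.* Step 4 shows that this does not follow. The first participant was randomised in March 2017 (Trial status), so a value not recorded at baseline cannot be recovered for women already enrolled.
- *Chance imbalance without stratification is a further harm.* The unadjusted variance 2σ²/n is the sum of an imbalance part, R² × 2σ²/n, and a residual part, (1 − R²) × 2σ²/n. The t test's standard error already contains the first part. It is the same precision loss, not a bias on top of it.
- *The primary result is weakened.* The primary outcome is binary and has its own test and sample size. Nothing here bears on either.

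**Conclusion.** The point holds as an optional efficiency improvement of low severity. The stated t test is sound, but it leaves unused a baseline variable that every participant has. Under an assumed R² of 5% to 30%, adjustment would shorten the intervals for the two counts by about 2.5% to 16%. With age alone the gain may sit at or below the low end; the article gives no basis for saying where. The conclusion needs only that some baseline variable is related to the outcome. Its size rests wholly on the assumed R².

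**What to change.** In the analysis plan, before outcomes are examined by arm, state that the main analysis of oocytes retrieved, and separately of viable embryos, is a linear regression on arm and age (continuous) in all randomised women. Use robust standard errors and report the adjusted mean difference with its 95% confidence interval. Add one named reserve measure, either antral follicle count or anti-Müllerian hormone, only if baseline records show that it was taken before randomisation for essentially all women. Settle this without reference to outcomes. Keep the t test as a sensitivity analysis.

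The cost is a few sentences of wording and one check of baseline records. Age is already held, so adjusting for it needs no new data, and no procedure, treatment or sample size changes. The rule for counting cycles without a retrieval is a separate matter, needed equally for the t test and the regression.
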